**3.3 Subject withdrawal/discontinuation criteria:**

1. Inappropriate enrollment. Those who have not received any treatment after enrollment should withdraw immediately, and the subject's information will not be included in the study analysis. If the subject has already received study treatment, the investigator will evaluate the subject and determine the benefit and risk of the subject before deciding whether to withdraw. If the subject needs to be excluded, he/she will be withdrawn from the study after the completion of follow-up after treatment. The subject’s information will not be included in the efficacy analysis of this study, but should be included in the safety analysis.
2. Any of the following situations occur during the pre-treatment evaluation stage: new or deteriorated systemic disease which meet the exclusion criteria, voluntarily withdraw consent or lost to follow-up or death; poor compliance.
3. For those who are considered to be excluded by investigators, the investigator shall report the reasons for the exclusion to the principal investigator. When permitted, patients who have not yet received any study treatment should be withdrawn immediately, and the information of this subject will not be included in the study analysis. If the subject has already received the protocol specified treatment, he/she will be withdrawn from this study after the completion of the follow-up after treatment, and the subject will not be included in the efficacy analysis of this study, but should be included in the safety analysis.
4. Subjects may request withdraw from the clinical trial at any time during the study period if they do not want to continue.
5. If serious adverse events occur, the subject might be withdrawn on the judgment of the investigator.
6. Deterioration during the trial, which may threaten the life of the subject, or other conditions that may affect the observation appear during the trial.
7. The subject lost follow-up or die during the treatment period.
8. The subject received chemotherapy, Chinese medicines, other immunotherapy drugs, radiotherapy sensitizers, or other drugs that affect the efficacy and toxicity evaluation during the trial.
9. Serious deviations which makes it difficult to evaluate the drug effect.
10. Poor compliance.
11. **Study plan and timing of procedures**

[figure not shown]

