**2.1 Primary objective:**

**Overall Response Rate (ORR):** Tumor response is evaluated by investigators according to the Response Evaluation Criteria in Solid Tumors (RECIST) 1.1. ORR is defined as the proportion of patients who experienced CR or PR as the best response in the total evaluable cases.

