**6 Statistical analysis**

**6.1 Calculation of sample size**

This study uses the objective response rate (ORR) as the primary end point. This single-arm study requires 56 eligible patients. Considering a 10% dropout rate, a total of 63 patients will be enrolled.

The research hypothesis is based on Checkmate 017 and Checkmate 057 study, which reported an ORR of 20%. If the ORR of the experimental treatment in this study is 20%, it is not worthy of further study. But if the ORR of the experimental treatment in this study is 38%, the study is considered successful. The purpose of this study is to distinguish ORR between 20% and 38%. The statistical assumptions are: the null hypothesis ORR<=20%, and the opposite hypothesis ORR>=38%. If 17 or more of the 56 eligible patients are CR or PR, this study is deemed successful and is worthy of further study. With a one-sided type one error rate (alpha) equal to 0.0432, this study has at least 90% statistical power to reject the null hypothesis.

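### Treated patients can be dropped from the efficacy analysis on investigator judgement after follow-up, so the stated error rate and power of the 17-of-56 rule are not secured

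*Protocol*

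**What the plan says.** Protocol section 3.3 lists grounds for withdrawal. Two of them state what happens to the efficacy data of a patient who has already received study treatment:

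- Item 1 concerns inappropriate enrolment. The investigator weighs benefit and risk and decides whether the treated patient is withdrawn. A patient who is excluded is left out of efficacy and kept in safety.
- Item 3 concerns patients whom investigators consider should be excluded. No criteria are listed. The reason is reported to the principal investigator, the treated patient leaves once post-treatment follow-up is complete, "and the subject will not be included in the efficacy analysis of this study, but should be included in the safety analysis".

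Section 2.1 has investigators assess response by RECIST 1.1 and defines ORR as "the proportion of patients who experienced CR or PR as the best response in the total evaluable cases". Section 6.5.1 uses the same denominator. The title describes the trial as open-label.

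Section 6.1 sets the test. The number needed: "This single-arm study requires 56 eligible patients". The null is an ORR of 20% or less and the alternative 38% or more. The success criterion: "If 17 or more of the 56 eligible patients are CR or PR, this study is deemed successful". The error rate is given as 0.0432, one-sided. The power claim: "this study has at least 90% statistical power to reject the null hypothesis". On enrolment: "Considering a 10% dropout rate, a total of 63 patients will be enrolled". No cut-off is given for any number other than 56.

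**The concern.** ORR is the only primary endpoint, and the 17-of-56 count is the only success rule. Under item 3, the people who read the scans can also propose that a treated patient be left out of the efficacy analysis, at a time when the response can already be known. If the patients left out are more often non-responders, the reported ORR rises and an ineffective regimen is more likely to be declared worth further study. With no control arm, nothing offsets that bias.

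A second, smaller weakness adds to this. With 63 enrolled and an evaluable denominator, the analysed number will often differ from 56, and the error rate and power in section 6.1 belong to 56 only.

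**Working it through.** **Inputs, all from Protocol section 6.1:** n = 56, cut-off 17, null ORR 20%, alternative 38%, dropout 10%, 63 enrolled. The shares of treated patients removed in step 3 are assumptions; the only related figure in the document is the 10% dropout allowance.

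**1. Reproduce the plan's figures.** With X binomial:
- Alpha = P(X ≥ 17 | n = 56, p = 0.20) = 0.0432, as stated.
- Power = P(X ≥ 17 | n = 56, p = 0.38) = 0.9076, consistent with at least 90%.
- Enrolment = 56 / 0.9 = 62.2, rounded up to 63, as stated.

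**2. What these figures require.** Exactly 56 patients must be analysed, and whether a patient is analysed must not depend on response.

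**3. Exclusion that depends on response.** Let the true ORR be 20% in all treated patients and let a share d of treated patients be removed, all of them non-responders. The ORR among those left is 0.20 / (1 − d). With 56 analysed:

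| d (assumed) | ORR among those left | P(≥ 17 of 56) |
|---|---|---|
| 0 | 20.0% | 0.0432 |
| 2.5% | 20.5% | 0.0533 |
| 5% | 21.1% | 0.0656 |
| 10% | 22.2% | 0.0990 |

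Upper bound: suppose all 63 are treated and 7 non-responders are removed, leaving 56. No responder is lost, so success needs 17 responders among 63: P(X ≥ 17 | n = 63, p = 0.20) = 0.112. An observed 17/63 = 27.0% is then reported as 17/56 = 30.4%.

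**4. Analysed number other than 56, no selection.** If the cut-off stayed at 17:

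| n | Alpha (p = 0.20) | Power (p = 0.38) |
|---|---|---|
| 50 | 0.0144 | 0.765 |
| 53 | 0.0259 | 0.849 |
| 56 | 0.0432 | 0.908 |
| 57 | 0.0505 | 0.922 |
| 60 | 0.0772 | 0.956 |
| 63 | 0.1120 | 0.976 |

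The direction changes at 56: above it alpha rises, below it the rule is conservative and power falls short of 90%.

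**5. Cut-offs matched to n.** The smallest count with exact one-sided tail probability ≤ 0.05 against 20% is 16 for n = 49–52, 17 for 53–56, 18 for 57–61 and 19 for 62–63. At n = 63 the cut-off of 19 gives alpha 0.0362 and power 0.923.

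**6. Matching the cut-off does not cure selection.** With 63 treated and 3 non-responders removed, n = 60 and the matched cut-off is 18, but the true false-positive rate is P(X ≥ 18 | n = 63, p = 0.20) = 0.066. With 7 removed it is again 0.112.

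**7. Cost of counting non-evaluable patients as non-responders.** If ORR is 38% among evaluable patients and k of 63 treated are not evaluable, the ORR in all treated is 0.38 × (63 − k) / 63. Power at 19 of 63:
- k = 0: rate 0.380, power 0.923.
- k = 3: rate 0.362, power 0.871.
- k = 7: rate 0.338, power 0.768.

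**The case against.** Several points on the other side are sound and limit the finding.

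- Section 6.1 contains no arithmetic error. A reader might infer that 0.0432 is wrong; it is exactly right for the rule as written, and the criticism is that other sections do not secure its conditions.
- A reader might infer from the rest of section 3.3 that patients who deteriorate, die, are lost, take other therapy or comply poorly (items 6, 7, 8 and 10) are also removed from efficacy. The text does not say so. Those are withdrawal grounds; only items 1 and 3 state an efficacy exclusion. Such patients might fall outside the evaluable denominator, but that is conjecture.
- A reader might infer that 17 is to be applied to 57–63 patients. The protocol does not direct this; it is silent on any n but 56. The alphas above 56 show only that the single cut-off does not carry over.
- The 0.112 needs all 7 patients in the dropout allowance to be treated, removed and non-responders. The allowance may include never-treated patients, whose exclusion is not at issue here.
- Item 1 concerns eligibility, and item 3 requires the reason to be reported. Exclusion on baseline facts alone would be less serious. Reporting a reason is a weak control, because it limits neither the grounds nor the timing.
- Defining the evaluable set and adapting the cut-off could be left to an SAP that is not shown. That answers silence, but not items 1 and 3, which state the exclusion outright; an SAP counting every treated patient would contradict them.
- This is a phase II screen, not a confirmatory claim. Even so, the rule affected is the trial's only success criterion.

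**Conclusion.** The point stands in this form: item 3, and item 1 once treatment has begun, permit removal of treated patients from the primary analysis on investigator judgement, and under item 3 without criteria and when response can be known. The 0.0432 is therefore not guaranteed; it has not been shown to be false. Depending on how many non-responders are removed, the false-positive rate runs from about 0.05 to 0.10 for assumed removal of 2.5% to 10% of treated patients, with 0.112 as the bound when 63 are treated, the cut-off is 17 and no responder is removed. The documents do not show that selective removal will happen, or how much. Nor does the error rate always rise: with fewer than 56 analysed, unselected patients and a cut-off of 17, it falls and the loss is in power.

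**What to change.** - Delete the efficacy exclusions for treated patients in section 3.3 items 1 and 3. Alternatively, limit them to ineligibility on pre-treatment facts, judged without knowledge of response.
- In sections 2.1 and 6.5.1, make the primary ORR set all treated patients, or all eligible treated patients, with those lacking an assessable response counted as non-responders. Keep the evaluable set as a sensitivity analysis.
- In section 6.1, replace the single cut-off with one tied to the number analysed by the exact one-sided binomial at ≤ 0.05 against 20%: 16 for 49–52, 17 for 53–56, 18 for 57–61, 19 for 62–63. This must accompany the first two changes, since it does not remove selection bias.
- Restate the power.

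The changes are to wording and need no extra patients in themselves. The cost is that treated non-evaluable patients count against the regimen: with 38% ORR among evaluable patients, power at 19 of 63 is 0.92 with none, 0.87 with 3 and 0.77 with 7. If the full 10% allowance is expected to be treated but non-evaluable, the 90% claim cannot be kept at 63 patients; either it is lowered or the sample size is reconsidered.

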**Figure 1. Study flow**

**Table 1. Study schedule**

|  | **Baseline screening** | **SBRT** | **Sintilimab, GM-CSF treatment** | **Sintilimab maintenance** | | **End of treatment**  **Survival follow-up** |
| --- | --- | --- | --- | --- | --- | --- |
| Window (days) | Within 28 days before the start of SBRT | End of SBRT  (or before D1 administration) | C1D1  D5/9/14 (± 2 days) | C2D1  (±3 days) evaluation before each administration | CnD1  (±3 days) | Every 3 months  (±7 days) |
| Frequency |  |  | 3 times in total | Every 3 weeks | Every 9 weeks  (every 3courses of Sintilimab) | Every 3 months |
| **Research procedure** |  | | | | | |
| Informed consent^1^ | X |  |  |  |  |  |
| Inclusion criteria | X |  |  |  |  |  |
| Demography/ Medical history/ Previous treatments^2^ | X |  |  |  |  |  |
| Vital signs ^3^ |  |  |  |  |  |  |
| Weight/Height^4^ | X |  |  | X | X |  |
| Medical history^5^/ Physical examination | X |  | X | X | X | X |
| ECOG PS score | X |  |  | X | X | X |
| Blood routine ^6^ | X |  | X | X | X | X |
| Coagulation function ^7^ | X |  |  | X | X | X |
| Blood Biochemistry ^8^ | X |  | X | X | X | X |
| Thyroid function ^9^ | X |  |  | X | X | X |
| Pregnancy test ^10^ | X |  |  |  |  |  |
| Urinalysis ^11^ | X |  |  | X | X |  |
| Virological antibody testing (HIV, HBV and  HCV) | X |  |  |  |  |  |
| 12-lead ECG | X | when necessary | | | | |
| Lung function | X |  |  |  |  |  |
| Adverse event assessment ^12^ |  | X | X | X | X | X |
| Concomitant medication | X | X | X | X | X | X |
| Subsequent anti-tumor treatment |  |  |  |  |  | X |
| Telephone follow-up (when outpatient follow-up is not possible) |  |  |  |  |  | X |
| **Efficacy evaluation** |  | | | | | |
| Radiographic assessment ^13^ | X |  |  |  | X | X |
| Gene mutation detection ^14^ | X |  |  |  |  |  |
| **Biomarker exploration** |  | | | | | |
| Blood specimens for biomarker studies ^15^ | X | X (end of SBRT) | X | X | X | X |
| Tumor puncture ^16^ | X | X (end of SBRT)  (Recommended, not required) | X (after d14 GM-CSF medication,  Recommended, not required) |  |  |  |

1. The signing of the ICF should be performed before any study procedure.
2. Previous treatments include treatment for the initial diagnosis, including chemotherapy, radiotherapy, and surgical treatment, as well as treatment for previous co-existing diseases within the past 30 days.
3. Vital signs include temperature, pulse, respiratory rate, and blood pressure.
4. Height measurement is only performed during the screening period. Weight of subjects is measured before each administration. If the weight of the subject fluctuates less than 10% from the baseline (the day of the first study dose), the baseline weight is used to calculate the dose of chemotherapeutic drugs. Otherwise, the actual dose is calculated according to the body weight on the day of the planned administration.
5. Medical history must include medical and surgical history, history of smoking/alcohol consumption/family history, previous radiotherapy and chemotherapy, and symptoms of intracranial hypertension.
6. Blood routine includes red blood cell count (RBC), hemoglobin (Hb), white blood cell count (WBC), and white blood cell count (absolute neutrophil count and absolute lymphocyte count are required), hematocrit (HCT), platelets (PL).
7. Coagulation functions include PT and INR. It is carried out within 28 days before the first study dose during the screening period and during the safety follow-up. The lab tests are carried out in various research centers.
8. Blood biochemistry includes blood electrolytes (K, Na, Ca, Mg, Cl, HCO_3_^-^ are required), ALT, AST, γ-GT, total bilirubin, direct bilirubin, amylase, lipase, creatinine, urea nitrogen, serum albumin, blood glucose.
9. Thyroid function includes T3, T4, fT3, fT3, TSH.
10. Women of child-bearing age should undergo a urine or serum pregnancy test within 28 days before the first dose in the screening period. If the urine pregnancy test result cannot be confirmed as negative, a serum pregnancy test should be performed, and the serum pregnancy result shall prevail. Tests will be carried out in various research centers.
11. Urinalysis must include urine specific gravity (SG), urobilinogen (URO), occult blood (BLD), white blood cells (WBC), urine protein (PRO), urine glucose (GLU), bilirubin (BIL), ketone bodies (KET), urine red blood cells (RBC), urine color (COL).
12. The assessments of AE and laboratory test safety are evaluated according to CTCAE v 5.0. Definition, recording, relevance judgments, severity judgments, reporting time limits and management of AE and SAE are described in sections 5 and 7 of the protocol.
13. Imaging examinations at baseline screening include: Chest CT examination within 28 days before treatment. PET-CT can be used instead. Abdominal CT/MRI within 28 days before treatment. PET-CT can be used instead. Cranial MRI examination within 28 days before treatment. Patients with metal foreign bodies or implants that prevent them from receiving cranial MRI can receive enhanced skull CT instead. Whole-body bone scan within 28 days before treatment. Bone scan is excused if PET-CT shows negative bone metastases. PET-CT is not necessary. In the follow-up (once every 3 courses of Sintilimab), imaging examinations, except for the parts with local symptoms, only examine the location of the lesion at baseline, and the same imaging examination methods as the baseline should be used. The examination items for different sites are listed as follow: chest: chest CT, which can be replaced by PET-CT; abdomen: abdominal CT/MRI, which can be replaced by PET-CT; cranial MRI examination (optional): For patients with metastases shown by baseline cranial MRI/enhanced CT, this item is required at each subsequent efficacy evaluation. For patients with negative baseline brain metastases, this item is optional and is only required when there are symptoms. Whole-body bone scan (optional): It is performed for patients with only symptoms of bone metastasis or those who need to confirm CR. PET-CT is optional. Note: If new lesions are suspected at any site outside the follow-up, imaging examinations should be performed appropriately.
14. From the diagnosis of NSCLC to any time point before the enrollment of this treatment, the gene mutation detection of the primary and metastatic tumor can be performed, including EGFR (exon 18, 19, 20, 21) mutation, ALK and ROS-1 gene rearrangement.
15. Blood sample collection: All the following samples should be clearly marked with the clinical trial code, patient ID number, collection date and time, and sample type.

(1) One EDTA anticoagulation tube and one coagulation promoting tube of 10 ml venous blood should be collected, respectively.

(2) Plasma and PBMC from anticoagulant blood should be separated within 2 hours and stored at minus 80 degrees.

(3) Pro-coagulant blood is separated within 2 hours after collection, and stored at minus 80 degrees

1. Tumor tissue biopsy: all the following samples should be clearly marked with the clinical trial code, patient ID number, collection date and time, and sample type.
2. A 16-18G biopsy gun is used to take at least 5mm*5mm tumor tissues from the target lesions.
3. One piece is placed in formalin and sent to the pathology department for paraffin embedding;
4. The other one is placed in RNA later at 4°C overnight and then stored at minus 80°C for long-term storage.

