**5 Treatment**

The combination of SBRT with sintilimab and GM-CSF is applied. One lesion (primary or metastatic lesion) is selected for SBRT, with the dose of 24Gy/3Fx. Within Two weeks after SBRT is completed, Sintilimab and GM-CSF treatment are initiated and used in combination, with the date recorded as d1. GM-CSF is continuously used for 14 days (d1-d14) at the dose of 125 μg/m^2^. Sintilimab is administrated at the dose of 200 mg/time once every 3 weeks from d1 (d21n +1, n≥0), 35 cycles in total (2 years), or until the investigator deems that the patient needs to be discontinued due to treatment-related toxicity or disease progression. The overall response rate and toxicity were assessed periodically.

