**5.2 Sintilimab**

Starting on the second day (d1) after the completion of SBRT treatment, Sintilimab was given intravenously once every 3 weeks at a dose of 200 mg. Blood routine, blood biochemistry, coagulation function, and thyroid function should be checked before each administration, in order to evaluate the related adverse events. During each 3 courses of treatment (every 9 weeks), the efficacy is evaluated (according to the RECIST1.1), and the treatment is continued until disease progression, death, unacceptable toxicity or up to 35 cycles (2 years) or the patient withdraws informed consent. See 5.2.1-5.2.8 for the principles of Sintilimab use, withdrawal, resumption of medication, infusion reaction management, dose adjustment, toxicity management, concomitant treatment and drug management.

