**Table 3. Suspension and permanent withdrawal of Sintilimab**

a: Resume administration after the symptoms improved to grade 0-1 or baseline level.

b: For hypophysitis, adrenal insufficiency, thyroid insufficiency/hypothyroidism, and type 1 diabetes, Sintilimab can be restarted if they are fully controlled and require only physiological hormone replacement therapy.

c: For abnormal grade 4 laboratory test results, the decision to terminate the medication should be based on the accompanying clinical symptoms/signs and the clinical judgment of the investigator.

The maximum interval allowed for drug suspension is 12 weeks. If it is not possible to return to the state where Sintilimab can be re-used within 12 weeks, the subject will permanently stop Sintilimab and enter the follow-up phase. Except for the following two cases:

1. Due to the application of glucocorticoids in the treatment of irAE, the process of glucocorticoid reduction led to the suspension of Sintilimab for more than 12 weeks. In this case, it is necessary to discuss with the sponsor's medical manager to decide whether to continue Sintilimab treatment. The imaging examination to evaluate the efficacy is carried out as planned, and is not affected by the suspension of medication.

2. Sintilimab was suspended for more than 12 weeks due to treatment related AEs unrelated to Sintilimab. In this case, it is necessary to discuss with the sponsor to decide whether to continue Sintilimab treatment. The imaging examination to evaluate the efficacy is carried out as planned, and is not affected by the suspension of medication.

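### Efficacy imaging is scheduled both by course count and by calendar; for suspensions of up to 12 weeks the protocol does not say which governs, so compliant scans can fall anywhere from 9 to 21 weeks

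*Protocol*

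**What the plan says.** Four places bear on scan timing during treatment.

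- **Table 1, imaging footnote (13).** The frequency is in courses only: "In the follow-up (once every 3 courses of Sintilimab".
- **Table 1, body.** On-treatment radiographic assessment sits in the CnD1 (±3 days) column, a dosing visit. Its frequency row gives 9 weeks and adds in brackets "every 3courses of Sintilimab".
- **Section 5.2.** Both units appear together: "During each 3 courses of treatment (every 9 weeks), the efficacy is evaluated".
- **Notes under Table 3 (section 5.2.2).** "The maximum interval allowed for drug suspension is 12 weeks". Two numbered cases are then carved out ("Except for the following two cases"), both for suspensions longer than 12 weeks. Each ends with the same sentence: "The imaging examination to evaluate the efficacy is carried out as planned, and is not affected by the suspension of medication". No such sentence is given for suspensions of 12 weeks or less.

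Section 5.2.5 allows interruptions for reasons other than treatment-related adverse events, with restart within 3 weeks. It does not mention imaging. After treatment, Table 1 schedules imaging every 3 months (±7 days).

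**The concern.** Three courses of 3 weeks are 9 weeks only if every dose is on time. Once a dose is suspended, a site counting courses and a site counting weeks will scan on different dates, and both are following the protocol. The rule that would settle this is written only for the longest suspensions.

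PFS runs to the first documented progression, so its value depends on when scans are done. Suspensions are mostly triggered by toxicity, so any shift falls on patients who tolerate treatment poorly and may vary by centre. With a single arm, no control group shares the shift.

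**Working it through.** **1. The protocol's own equivalence.** Section 5 gives the dosing grid: "once every 3 weeks from d1 (d21n +1, n≥0), 35 cycles in total (2 years". Three courses × 3 weeks = 9 weeks. The stated interval reproduces when there is no delay.

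**2. The two clocks after a delay.** Calendar reading: interval = 9 weeks. Course reading: interval = 9 + D, where D is the delay in weeks within the three-course block. If progression is spread evenly over the interval, the mean wait to the next scan is half the interval.

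| Delay D (weeks) | Calendar interval | Course interval | Mean wait, course reading |
|---|---|---|---|
| 0 | 9 | 9 | 4.5 |
| 1 | 9 | 10 | 5.0 |
| 3 | 9 | 12 | 6.0 |
| 6 | 9 | 15 | 7.5 |
| 12 | 9 | 21 | 10.5 |

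The last row is the longest ordinary suspension. Placed before course 4, it moves the first efficacy scan from week 9 to week 9 + 12 = 21.

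**3. Effect on recorded PFS.** The protocol gives no suspension frequency or length, so these are assumptions: exponential true PFS with a median of 4 to 6 months (4.345 weeks per month); 10% or 30% of patients with one suspension of 3-12 weeks, starting in weeks 3-18; no unscheduled scans. Progression is recorded at the next scan on each clock, and the two dates are compared in a simulation of 400,000 patients.

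- Delayed patients: recorded on average about 1.3-1.8 weeks later on the course clock, at most 12 weeks.
- All patients: share delayed × mean lag. The low end is 0.10 × 1.35 = 0.1 weeks and the high end is 0.30 × 1.8 = 0.5 weeks.
- About 29-35% of delayed patients are recorded earlier. For example, a 3-week suspension starting at week 12 moves the week-18 scan to week 21. Progression at week 20 is then recorded at week 21 instead of week 27, while progression at week 16 is recorded at week 21 instead of week 18.

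**4. Effect on the median.** With a true median of 4 months (4 × 4.345 = 17.4 weeks), the recorded median goes from 18 to about 21.5-24.5 weeks. With 6 months (26.1 weeks), it goes from 27 to 27-29.4 weeks. At 4.5, 5 and 5.5 months it stays at 27. At 4.2 months with 30% delayed it falls from 27 to about 26.5. The cause is the 9-week grid. At 4 months, 1 − 2^(−18/17.4) = 51% have progressed by week 18, so a very small shift takes the median off that step. The 6-month case sits just before week 27 in the same way.

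**5. Primary endpoint.** The exact binomial rule of 17 or more responses in 56, with 20% against 38%, gives one-sided alpha 0.0432 and power 0.9076; 56/0.9 rounds up to 63. All match section 6.1, and none depends on the scan interval.

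**The case against.** The calendar figure is in the text. Table 1's frequency row leads with 9 weeks and puts courses in brackets, section 5.2 repeats it, and only the footnote uses courses alone. The dosing formula counts from d1 and does not say that a missed dose shifts later courses. The sentence in the two exceptions also points to the calendar: early in a suspension nobody knows whether it will exceed 12 weeks, so imaging can stay on plan in those cases only if it was not held back before. Imaging is required when new lesions are suspected, and interruptions under section 5.2.5 should end within 3 weeks. PFS is described by Kaplan-Meier curves, with no test or success threshold.

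Much of this stands. A reader might infer that the protocol ties scans to courses, so that dose delays do postpone detection of progression. The documents do not support that as a rule; it is one of two available readings. A reader might also infer that median PFS is inflated by several weeks. Step 4 shows that such jumps occur only where the true median lies just before a scan date.

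The ambiguity itself remains. The sentence on suspensions is not written for the common cases, and its reference to the plan leads back to a plan in two units. Unscheduled scans depend on suspicion of new lesions and will not reliably catch silent growth of known ones.

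**Conclusion.** The point holds as an ambiguity of units. For suspensions of up to 12 weeks and for the interruptions in section 5.2.5, the protocol does not say whether weeks or courses govern imaging. A single maximal suspension allows anything from 9 to 21 weeks.

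The likely effect on PFS is modest: 0.1-0.5 weeks on average over all patients and 1.3-1.8 weeks in delayed patients, in either direction for individuals. The median shift depends on the grid and is often zero. These sizes rest on the assumed suspension pattern, exponential PFS and no unscheduled scans. Nothing in the documents supports a claim that the ORR test, sample size or power is affected. This is a cheap improvement to a descriptive secondary endpoint, not a threat to the trial's main conclusion.

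**What to change.** In Table 1, its imaging footnote and section 5.2, state that efficacy imaging during the treatment period is done every 9 weeks by calendar from d1, within a stated window, regardless of delayed or missed courses. Move the sentence on imaging during suspension out of the two exceptions, so that it covers all suspensions in section 5.2.2 and the interruptions in section 5.2.5.

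Limit the change to the treatment period. Wording that ran until progression whatever the treatment status would override the 3-monthly imaging of the follow-up phase and add scans.

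The cost is wording only: the planned interval is unchanged and no dosing rule is touched. In patients with delays, some scans will not coincide with a dosing visit.
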